### Sample size

In the main analysis, we aim to validate and re-calibrate the risk algorithm implemented in the **arriba**-software for primary prevention. To quantify the impact of a predictor, at least 10 events are needed [22]. If we assume patients in our cohort to have an average risk of a cardiovascular event of 5% in 10 years, the study of 9 predictors (see Table 1) would require a sample of at least 1,800 patients. However, further analyses will require a higher sample size. To validate the risk algorithm within the subgroup of patients with a known coronary heart disease a total sample size of 3,000 patients would be required if we assume that the percentage of this subgroup is 10% of the total sample and that the average risk of a cardiovascular event within this group is 30% in 10 years. Adjusting for the risk-modifying effect of treatment will raise the number of covariates to be entered in the models and the sample size accordingly. Within the first two years, 466 GPs have recruited about 4,100 patients. Considering a total time of enrolment of 4 years, the resulting sample size will meet our requirements with a sufficient safety margin.

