### Ethics and funding

The study complies with the Declaration of Helsinki. The research protocol was approved by the ethics committee at the University of Marburg (ID 159/11). All patients who participate in the HzV AOK BW are asked to give their written consent for personal data to be used for research purposes.

A grant provided by the AOK allows a five years’ study duration. However, funding for an extended study period will be sought.

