We are aware that in order to adapt and validate a ten-year cardiovascular risk calculator an extended follow-up period will be needed. Evidence based on shorter follow-up periods will be only preliminary. We therefore aim at longer follow-up than the five-year period that we have obtained funding for so far.

Despite these limitations, the study presented here provides an unusual opportunity to improve cardiovascular risk prediction for primary care. Simulation of a therapy naïve cohort, the exact match of research and application setting, a robust administrative database, and, finally, the inclusion of patients with known cardiovascular disease make this study unique in comparison with previous adaptations of cardiovascular risk algorithms.

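### The patient requirements of 1,800 and 3,000, and the margin claimed over them, assume ten years of event risk per patient, but only a five-year study is funded

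*Protocol article*

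**What the plan says.** The Sample size section asks for at least 10 events per predictor. For the main analysis, in primary prevention, it assumes an "average risk of a cardiovascular event of 5% in 10 years" and concludes that "the study of 9 predictors (see Table 1) would require a sample of at least 1,800 patients". For patients with known CHD, "a total sample size of 3,000 patients would be required if we assume that the percentage of this subgroup is 10% of the total sample", with an average 10-year risk of 30% in that group. It adds that adjusting for treatment will increase the covariates and the sample needed, without giving a number. About 4,100 patients joined in the first two years, and the section ends: "Considering a total time of enrolment of 4 years, the resulting sample size will meet our requirements with a sufficient safety margin".

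On duration, the Ethics and funding section says: "A grant provided by the AOK allows a five years" of study duration. Money for a longer period is still to be sought. The Discussion accepts that a ten-year calculator needs longer follow-up: "Evidence based on shorter follow-up periods will be only preliminary".

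**The concern.** An events-per-predictor rule is met by observed events, and events accrue only while patients are followed. The section converts its event target into patients as if each would be watched for ten years, then compares the result with a head count at the end of four years of enrolment. The margin sentence carries no condition on follow-up, and the Discussion's caveat is never taken back to it.

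A reader or funder would conclude that the funded study comfortably supports both analyses. The CHD subgroup matters most here, because the Discussion presents a calculator for patients with known disease as a result of the study. The Data analysis section also plans to adjust the base risk of a 10-year algorithm, which no more than five funded years per patient can observe directly.

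**Working it through.** **Inputs from the protocol article.** Sample size section: 10 events per predictor, 9 predictors, 10-year risks of 5% (main) and 30% (CHD), CHD share 10%, about 4,100 patients in two years, four years of enrolment. Ethics and funding section: five-year study duration.

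**Assumptions of this check, not stated in the protocol.** Recruitment continues evenly to 2 × 4,100 = 8,200; hazards are constant; there are no losses; the five years include enrolment. Follow-up is then uniform on 1 to 5 years, mean 3.

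**1. The plan's own figures.** Events needed: 9 × 10 = 90.
- Main: 90 / 0.05 = 1,800.
- CHD: 90 / (0.10 × 0.30) = 3,000.

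Both reproduce exactly, and only with the full 10-year risk. Against 8,200 patients the apparent margins are 8,200 / 1,800 = 4.6 and 8,200 / 3,000 = 2.7.

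**2. Risk over the funded period.** Hazard h = −ln(1 − r) / 10, which is 0.00513 per year (main) and 0.0357 per year (CHD). Mean event probability over uniform 1 to 5 years: 1 − (e^(−h) − e^(−5h)) / (4h), which is 1.525% and 10.07%.

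**3. Expected events at 8,200 patients.**
- Main, all patients counted: 8,200 × 0.01525 = 125.
- Main, only the 90% without CHD: 7,380 × 0.01525 = 113.
- CHD: 820 × 0.1007 = 83.

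**4. Requirements on the same basis as the plan's.**
- Main: 90 / 0.01525 ≈ 5,900. Margin 8,200 / 5,900 = 1.39, or 113 / 90 = 1.25 if only patients without CHD count.
- CHD: 90 / (0.10 × 0.1007) ≈ 8,940. Margin 83 / 90 = 0.92.

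**5. If every patient had five full years.** The risks become 2.53% and 16.33%. Requirements: 90 / 0.0253 ≈ 3,550 and 90 / 0.01633 ≈ 5,510. Expected events: 187 to 208 (main) and 134 (CHD).

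| Follow-up | Main: patients needed | Main: events at 8,200 | CHD: total patients needed | CHD: events at 8,200 |
|---|---|---|---|---|
| 10 years each (plan) | 1,800 | 369–410 | 3,000 | 246 |
| 5 years each | 3,550 | 187–208 | 5,510 | 134 |
| 1–5 years, mean 3 | 5,900 | 113–125 | 8,940 | 83 |

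**6. Added model terms.** Each needs 10 more events. With 1 to 5 years of follow-up, 113 to 125 events support 11 to 12 terms in the main analysis. The Data analysis section names two drug classes as examples and also intends to specify interactions. Nine predictors plus two drug terms need 110 events; one interaction brings this to 120. In the CHD subgroup, 83 events support 8 terms.

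**7. Sensitivity of the CHD count.** Linear risk (820 × 0.30 × 3/10) gives 74. If 6,000 patients rather than 4,100 join in the second two years, the count is about 96.

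**The case against.** Four points can be made for the plan.

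- **The need for longer follow-up is disclosed.** The Discussion calls earlier evidence preliminary, and further funding will be sought. A 10-year risk is a natural basis for a 10-year tool. This stands as disclosure. It does not qualify the margin sentence, which is unconditional, and the extension is not secured.
- **The duration can be read more generously.** The Discussion speaks of longer follow-up than the funded five-year period, which could be taken as five years for every patient. Both 90-event targets would then be met. The wording on the grant favours a total study duration, but the article does not settle the matter. On either reading 1,800 and 3,000 are too low for the funded period.
- **The CHD shortfall is small.** Seven events is less than one Poisson standard deviation (√83 ≈ 9). It closes if the CHD share is 10.9% (10% × 90 / 82.6) rather than 10%, or with faster recruitment. This stands, although losses and deaths from other causes would push the count down.
- **Treatment covariates are mentioned.** The section says they raise the requirement. It gives no number, so how far they use up the remaining margin cannot be fixed from the document.

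A reader might infer that no margin is left at all, or that the study cannot meet its own rule. The documents do not support this: on the stricter reading of follow-up, the main analysis with 9 predictors still expects 113 to 125 events against 90.

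**Conclusion.** The point holds as a defect of the sample-size statement. Its division is correct, but it applies a ten-year risk to a funded period of five years. With 1 to 5 years of follow-up, the requirements are about three times those stated (5,900 / 1,800 = 3.3; 8,940 / 3,000 = 3.0). With five years for everyone, they are still nearly double (3,550 / 1,800 = 2.0; 5,510 / 3,000 = 1.8).

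Under the mean-3-year reading, the main analysis keeps a modest margin of about 25 to 39% with 9 predictors, and the CHD analysis is borderline. A firm claim that the CHD analysis will fail would go too far, since it depends on the assumed 8,200 patients, the 10% share, constant hazards, no losses and the reading of the grant period. That the claimed margin depends on follow-up not yet funded rests on the protocol's own risks and durations, and that needs correcting.

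**What to change.** In the Sample size section:

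- State the requirement in events: 90 for 9 predictors, plus 10 for each further treatment covariate or interaction, with the intended number of terms.
- Give the events expected at the end of the funded period, with assumptions and range. On the plan's own rates these are about 113 to 125 (main) and 83 (CHD) with mean 3 years, and 187 to 208 and 134 if every patient has five years. Say which follow-up applies.
- Make the closing sentence on the margin conditional on extended follow-up.
- State there that CHD results from the funded period are preliminary, in line with the Discussion.

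For the analysis at the end of funding, compare observed events with those the current algorithm predicts over each patient's actual follow-up, and do not present a re-estimated 10-year base risk from those data.

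The cost is a less favourable stated margin and some rewording. No extra patients are needed.

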### Ethics and funding

The study complies with the Declaration of Helsinki. The research protocol was approved by the ethics committee at the University of Marburg (ID 159/11). All patients who participate in the HzV AOK BW are asked to give their written consent for personal data to be used for research purposes.

A grant provided by the AOK allows a five years’ study duration. However, funding for an extended study period will be sought.

## Discussion

The main aim of the cohort study outlined here is the validation and adaptation of a cardiovascular risk algorithm.

Cardiovascular risk algorithms have repeatedly been shown to have limited predicting power when tested on independent samples [10,23]. There are many reasons for this unsatisfactory state, among these biological variability, demographic, social, and cultural differences between derivation and validation cohorts, comorbidities, and intervention by health care providers outside the study protocol, to name just a few.

Our study does address three of these in an innovative way:

Simulation of a therapy-naïve cohort: The main goal of the **arriba** risk calculator is the unbiased information of individual patients in primary care practice. For individuals considering long-term interventions such as lipid or blood-pressure lowering therapy, predictive evidence should be based on cohorts without interventions modifying cardiovascular risk. However, this is unfeasible since most subjects in the cohort will be treated by their health care provider once a single risk factor or their global cardiovascular risk is found to be elevated. By accommodating drug therapy during follow-up we will be able to simulate a therapy-naïve cohort and thus provide risk estimates not biased by pharmacological interventions. To our knowledge this has not been attempted before.

Match between research and application setting: Previously developed cardiovascular risk algorithms were derived from geographically or occupationally defined populations. This puts a limit on their generalizability regarding counseling of individual patients in primary care. Our study sample, however, is drawn from exactly the population for which the algorithm will be used once the study is completed.

Inclusion of patients with known cardiovascular disease: Previously published risk algorithms were derived from populations free of overt cardiovascular disease. They can thus not be used to inform decision-making for secondary prevention. Against the background of aging populations with high prevalence of cardiovascular disease, this is a serious limitation. As a result of our study, a risk calculator applicable to this group will be available.

The automatic **arriba**-data-collection of patients who are enrolled in the GP centered health care contract (HzV) is an elegant way to obtain relevant data. Patients participating in the HzV tend to be slightly older and suffer from a higher morbidity burden when compared with those AOK insured, who are not enrolled in the HzV [24]. With the study design presented here we can describe the characteristics of each individual of our cohort and so will be able to adjust for possible confounders.

Selection bias may arise from selective use of **arriba** by participating GPs. As a result, certain groups would be underrepresented in our study sample because their GPs are not interested in their **arriba** risk. This would apply to patients at obviously very high or very low risk. However, we are confident that, given our sample size, these groups will still be sufficiently represented in our study. Moreover, educational measures have been implemented to encourage GPs using **arriba** in a broad range of patients. If on the other hand GPs use the decision tool **arriba** in a ‘selective’ way, then this is obviously the population they feel to be in need of the information provided by the software. As a result, a sample specifically adapted to the needs of future users would be assembled.

We will use administrative data of the AOK BW to assess relevant medication as well as cardiovascular events. These data can be expected to be highly valid since they are based on claims by pharmacies, hospitals and physicians [25]. An important data source will be the hospital claims data set. In Germany a diagnosis related groups (DRG) system is used for reimbursement of hospital services. In the German DRG system, not only the main diagnosis but also secondary diagnoses and main procedures are coded and used to determine the final DRG [26].

Our study design is not without limitations. Smoking status will only be evaluated at baseline, we will not be able to take changes in smoking habits during follow-up as well as other behavioral risk factors into account. The set of risk factors (predictors) is limited to those currently included in the **arriba** risk calculator.

We are aware that in order to adapt and validate a ten-year cardiovascular risk calculator an extended follow-up period will be needed. Evidence based on shorter follow-up periods will be only preliminary. We therefore aim at longer follow-up than the five-year period that we have obtained funding for so far.

Despite these limitations, the study presented here provides an unusual opportunity to improve cardiovascular risk prediction for primary care. Simulation of a therapy naïve cohort, the exact match of research and application setting, a robust administrative database, and, finally, the inclusion of patients with known cardiovascular disease make this study unique in comparison with previous adaptations of cardiovascular risk algorithms.

